#### **Applicability (feasibility) of the methods**

The feasibility of the methods (safety, side effects, rate of participant acceptance of applications), the feasibility of a full-scale study (target sample size, dropout rate, participation in targeted sessions) will be examined. The rate of falling out of the study should not be more than 20% and the participation in the sessions should not be less than 70%.

#### **Measuring autonomic functions**

Physiological responses as an indicator of autonomic function will be examined by measuring basal metabolic rate. A cardiopulmonary exercise test device will be used to measure physiological responses. For this purpose, Cosmed Quark CPET (Cosmed, Rome, Italy) branded device will be used in the Laboratory of Department Physiotherapy and Rehabilitation of Faculty of Health Sciences, İzmir Kâtip Çelebi University. This device provides a suitable mixing environment for gas exchange and instantaneous respiratory analysis ( $VO_2$ ,  $VCO_2$ ), 12-lead integrated electrocardiography monitoring, low and high ventilation ranges.

Each participant will be asked not to take food, caffeine, and nicotine at least 4 hours before. In addition, participants will be asked to avoid strenuous exercise 24 hours before the measurement (Vandarakis, Salacinski, & Broeder, 2013). The measurements will be taken while the participants are wearing comfortable clothing and lying on their backs on a stretcher. The room will be ventilated at least 1 hour before measurement and the room temperature will be kept at 20-23°C. Before measurement, the system will be calibrated to ensure that the  $O_2$  and  $CO_2$  gas concentrations are suitable for the test. All measurements will be taken in the morning.

During the measurement, the participant is put on a mask designed to contain his mouth and nose and will be asked to lie in bed for 15 minutes without doing anything. The system will automatically record data about the participant's metabolic expenditure at rest. These data are divided into three as metabolic, respiratory, and spent resources. Metabolic variables; caloric expenditure (RMR), oxygen uptake ( $VO_2$ ), carbon dioxide production ( $VCO_2$ ). Respiratory variables: ventilation (VE) is  $FeO_2$  and  $FeCO_2$ . The variables about the resources spent are fat, carbohydrate and protein.

|       |                                                                                                                                                                                                                                                                                                                                                                                                                                                                                                                                                                                                                                                                                                                                                                                                                                                                                                                                                                                                                                                                                                                                                                                                                                                                                                                                                                                                                                                                                                                                                                                                                                                                                                                                                                                                                                                                                                                                                                                                                                                                                                                                                                                                                                                                                                                                                                                                                                                                                                                                                                                                                                               |
|-------|-----------------------------------------------------------------------------------------------------------------------------------------------------------------------------------------------------------------------------------------------------------------------------------------------------------------------------------------------------------------------------------------------------------------------------------------------------------------------------------------------------------------------------------------------------------------------------------------------------------------------------------------------------------------------------------------------------------------------------------------------------------------------------------------------------------------------------------------------------------------------------------------------------------------------------------------------------------------------------------------------------------------------------------------------------------------------------------------------------------------------------------------------------------------------------------------------------------------------------------------------------------------------------------------------------------------------------------------------------------------------------------------------------------------------------------------------------------------------------------------------------------------------------------------------------------------------------------------------------------------------------------------------------------------------------------------------------------------------------------------------------------------------------------------------------------------------------------------------------------------------------------------------------------------------------------------------------------------------------------------------------------------------------------------------------------------------------------------------------------------------------------------------------------------------------------------------------------------------------------------------------------------------------------------------------------------------------------------------------------------------------------------------------------------------------------------------------------------------------------------------------------------------------------------------------------------------------------------------------------------------------------------------|
|       | 
Measures of motor imagery ability
 
1. Movement Imagery Questionnaire-Revised is a motor imagery questionnaire used in healthy adult and athletic populations and includes movements that require a high degree of skill and coordination (Butler et al., 2012). The visual and kinesthetic motor imagery skills of the person are measured with the scale consisting of 8 items. Items related to visual imagery are evaluated using a Likert-type scale between 1 (very difficult to see) and 7 (very easy to see). Items related to kinesthetic imagery are likewise evaluated using a Likert-type scale that is graded between 1 (very difficult to feel) and 7 (very easy to feel). High scores indicate high visual and kinesthetic imagery skills. The Turkish validation study of the questionnaire was conducted, and it was shown to be valid and reliable (Akkarpat, 2014).
 
2. Motor imagery skills will also be evaluated using a mental chronometry paradigm. The mental chronometry is based on measuring the temporal harmony between a real movement and the imagination of the same movement. Mental chronometry assessment will be applied for both lower and upper extremity movements. 6 m walking test will be applied for lower extremity. A 6 m line will be drawn on the ground with a mark at the beginning and end. Participants will be asked to imagine that they are walking this line at their normal speed from a first-person perspective (as if they were doing it themselves). Then the 6 m walking test will be applied in the form of real motion. Upper extremity of the participants for mental stopwatch test "Türkiye'nin başkenti Ankara" really leave behind you will be asked to imagine that they wrote the sentence. Participants will hold a digital stopwatch in their non-dominant hands during all tests and will start and stop time at the end of both real and imagined movement (Papaxanthis, Pozzo, Skoura, & Schieppati, 2002).
 
3. Hand lateralization judgment test
 
During this test, the participant is asked to indicate which hand shapes shown belong to the right or left hand. The high number of correct numbers is considered to be an indicator of high motor imagination (Boonstra et al., 2012). In this study, a tablet software (Recognise TM Flash Cards, NOI) with proven validity and reliability will be used (Zimney et al., 2018). During the test, different hand photographs of the tablet screen appear, and the participant is asked to choose which hand (right or left) the corresponding picture is.
 |
| C.3.8 | 
OPERATIONS AND VARIABLES TO BE USED IN THE RESEARCH
 
In this study, participants will be randomly assigned to one of three groups: Group 1: activating kinesthetic motor imagery training; group 2: relaxing kinesthetic motor
                                                                                                                                                                                                                                                                                                                                                                                                                                                                                                                                                                                                                                                                                                                                                                                                                                                                                                                                                                                                                                                                                                                                                                                                                                                                                                                                                                                                                                                                                                                                                                                                                                                                                                                                                                                                                                                                                                                                                                                                                                                                                                                                                                                                                                                                                                                                                                                            |

imagery training; and group 3: control group. After randomization and before the implementation, participants will be given an introductory training to become familiar with motor imagery. The concept of motor imagery and its uses in sports and rehabilitation will be explained. Different types of motor imagery (kinesthetic and visual) and perspectives (inner, first-person and outer, third-person perspective) will be explained theoretically and practically. Participants will be encouraged to practice on their own and be made aware of their preferred type and perspective of motor imagery. Emphasis will be placed on the use of internal and kinesthetic motor imagery in this study. Introductory training before motor image training is recommended by various authors (Schuster et al., 2011; Wondrusch & Schuster-Amft, 2013).

The PETTTLEP framework strategy based on a neuroscientific basis will be used for motor imagery. This strategy consists of Physical, Environmental, Task, Timing, Learning, Emotional and Perspective components (Holmes & Collins, 2001). PETTTLEP is a method developed to increase performance in athletes (Holmes & Collins, 2001). PETTTLEP elements include the practitioner's physical position according to the motor visualization task and perspective, the imagined environment, the imagined task, the timing of the motor imagery, learning or changes with motor imagery, and emotional states. PETTTLEP ideas will be applied in this pilot study to support participants' understanding of the application and effectiveness.

After the familiarization training and verbal instructions, the participants will be given DropBox links containing engine visualization training videos specially designed for their groups. Participants will be able to download the engine imagination training videos and instructions and watch them on their smartphones, computers, or tablets via these links. Participants will be asked to apply the kinesthetic motor imagery training at their own homes, 5 times a week, once a day for 17 minutes. The videos will be used to enable participants to see the exercises to accurately visualize the relevant movements. The frequency and duration of motor imagery sessions were decided according to the results of a review examining motor imagery training applied in different disciplines (Schuster et al., 2011). After a week, the participants will be called by phone, support will be provided for the application and will be reminded that there will be a post-implementation evaluation. The frequency of the application will be recorded in their exercise logs and they will be asked to report it on the phone. However, there will not be a direct exercise follow-up. Participants in the control group will not be given a special application but will be called by phone to remind the time of the second evaluation.

|        |                                                                                                                                                                                                                                                                                                                                                                                                                                                                                                                                                                                                                                                                                                                                                                                                                                                                                                                                                                                                                                                                                                                                                                                                                                                                                                                                                                                                                |
|--------|----------------------------------------------------------------------------------------------------------------------------------------------------------------------------------------------------------------------------------------------------------------------------------------------------------------------------------------------------------------------------------------------------------------------------------------------------------------------------------------------------------------------------------------------------------------------------------------------------------------------------------------------------------------------------------------------------------------------------------------------------------------------------------------------------------------------------------------------------------------------------------------------------------------------------------------------------------------------------------------------------------------------------------------------------------------------------------------------------------------------------------------------------------------------------------------------------------------------------------------------------------------------------------------------------------------------------------------------------------------------------------------------------------------|
| C.3.9  | 
STATISTICAL ANALYSIS
 
SPSS (version 24.0, IBM Corporation, Armonk, NY, ABD) software will be used in all statistical analyzes. The statistical significance level will be considered as two-sided <math>p < 0.05</math>. The compliance of the data to normal distribution will be evaluated by examining the results of skewness and kurtosis and histograms in addition to the Shapiro-Wilk test results.
 
Intention-to-treat analysis will be performed for all participants with follow-up data, considering the groups they were originally assigned to. Descriptive statistics will be used to summarize initial demographic variables.
 
The significance of the difference between pre-and post-training data will be analyzed in the dependent group using the t-test / Wilcoxon signed-rank test in accordance with the given distribution characteristics. Bonferroni correction will be used where necessary. Two-factor mixed pattern analysis of variance (ANOVA) will be used to examine continuous variables such that groups are a factor between participants and time is a factor for participants. Effect sizes will be calculated as partial eta square values. When a meaningful result is obtained in the relevant analysis, the reason for the difference will be examined with appropriate post hoc correction methods.
 |
| C.3.10 | 
RESEARCH PERIOD
 
Research start date: After the date of ethics committee approval.
 
The estimated duration of the study: 24 months.
                                                                                                                                                                                                                                                                                                                                                                                                                                                                                                                                                                                                                                                                                                                                                                                                                                                                                                                                                                                                                                                                                                                                                                                                                                    |

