|     | 
Duhamel, 2001). Motor imagery can also be defined as implicit or explicit (de Vries et al., 2013). Explicit motor imagery is defined as a phenomenological experience in which the sense of movement is experienced consciously (de Vries et al., 2013). That is, the individual is aware that he is imagining movement. On the other hand, implicit motor imagery is defined as unconscious visualization of movement (de Vries et al., 2013). For example, when an individual looks at a photograph of a hand standing in a different position than normal, he unwittingly imagines his hand gestures moving the hand to the position he is used to and decides whether the hand in the photograph is right or left. Open and closed motor visualization describe different aspects of cognitive task and should not be considered as separate situations from each other. A motor imagery task can be performed both visually and off, kinesthetic, and open, or vice versa (McInnes, Friesen, & Boe, 2016). However, motor imagery tasks used in neurorehabilitation are mostly explicit motor imagery, utilizing both kinesthetic and visual motor imagery (McInnes et al., 2016).
 |
| C.2 | 
RATIONALE/PURPOSE OF STUDY
 
Most of the studies on motor imagery attribute its mechanism of action to neuroplastic changes occurring in the brain (Gerardin et al., 2000; Kraeutner et al., 2014; Mulder, 2007; Schieber, 2013). On the other hand, it is thought that motor imagery can alter metabolic responses, just like in real exercise. In a study conducted on this subject, it was reported that physiological changes such as heart rate, oxygen consumption, blood pressure, respiratory rate, metabolic rate after motor imaging were like actual exercise (Wang & Morgan, 1992). However, the level of evidence for the effect of motor imagery on autonomic functions is extremely limited.
 
The aims of this study are;
 
 
1. To examine the effects of the activating and relaxing kinesthetic motor imagery training program on autonomic functions in healthy individuals and to compare these two methods with each other.
 
2. In the study, the effects of the mentioned training program on the motor imagery skills of individuals will also be examined.
 
  |

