|         | 
taken (Treece & Treece, 1982). Based on results from a previous motor imagery training study using physiological measurements (mean and standard deviation of heart rate differences between groups), the sample size of 63 participants per group was obtained using the HyLown sample size calculation software (http://powerandsamplesize.com/). Since there will be three groups in this study, it was determined that 189 participants were needed for a full-scale study. Based on these recommendations in the literature, it was decided that the sample size for this pilot study should be 15 participants per group. The total sample size was planned as 54 participants (18 per group), with the addition of possible losses of 20%.
 
Randomization
 
Participants will be divided into three groups using a simple randomization method based on a single sequence using computer software (https://www.randomizer.org/) by a researcher who will not be involved in evaluation and treatment (Altman & Bland, 1999).
 
Motor imagery training
 
DVDs containing motor imagery instructions will be given to the individuals participating in the motor imagery training. The same content will be made available for download online to participants (control) who wish to do so.
 
Group 1 will be trained in activating kinesthetic motor imagery. Scenarios in this motor visualization training will focus on exercises that require high effort (plank, boxing, jumping, crouching, push-up, etc.). In the motor imagery scenarios of the participants in Group 2, low intensity (relaxation) exercises (breathing exercises, stretching, body awareness exercises, etc.) will be included. Motor imagery training for both groups, 5 days a week, 17 minutes a day. It will be applied for 2 weeks (Schuster et al., 2011).
 |                                     |

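### Aim 1 is about autonomic function, but its only listed measures are metabolic, ventilatory and substrate variables; heart rate, the basis of the full-scale sample size, is not a listed outcome.

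*Protocol*

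**What the plan says.** C.2 gives the first aim as "To examine the effects of the activating and relaxing kinesthetic motor imagery training program on autonomic functions in healthy individuals", together with a comparison of the two programmes. The same section reports, from an earlier study, that imagery changed heart rate, oxygen consumption, blood pressure, respiratory rate and metabolic rate in a way similar to real exercise. It adds that evidence on autonomic function is very limited.

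In C.3.7, under the heading on measuring autonomic functions, the operational definition is: "Physiological responses as an indicator of autonomic function will be examined by measuring basal metabolic rate". The participant wears a mask and "will be asked to lie in bed for 15 minutes without doing anything". On the recorded output the protocol says: "These data are divided into three as metabolic, respiratory, and spent resources". The metabolic list begins "Metabolic variables; caloric expenditure (RMR), oxygen uptake" and adds VCO2. The respiratory list is VE, FeO2 and FeCO2. The third class is fat, carbohydrate and protein. The device description mentions "12-lead integrated electrocardiography monitoring", but no variable is taken from it.

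Under Sample size in C.3, the full-scale calculation of 63 per group (189 for three groups) rests on the "mean and standard deviation of heart rate differences between groups" in a previous imagery study.

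**The concern.** The aim and the measure are on different footings. The aim names a function of the nervous system. The measure is resting energy expenditure with its gas-exchange components. The protocol joins the two with the word indicator and gives neither an argument nor a validation source. The one source cited in that section is, by its title, a comparison of metabolic systems for determining resting metabolic rate.

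Two things are at stake. First, a group difference in RMR or VO2 would be reported as an autonomic effect, and the lack of one as the absence of an autonomic effect, when the data show only a difference, or no difference, in resting metabolism. Second, the feasibility section of C.3.7 counts the target sample size among the matters to be examined for a full-scale study. The only full-scale calculation in the protocol uses heart rate, and the pilot does not list heart rate among the variables it will report. A later analysis plan cannot repair either gap if the data were never collected.

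**Working it through.** **Step 1: the aim against the listed measures.**

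| Class in C.3.7 | Variables | Cardiovascular measure? |
|---|---|---|
| Metabolic | RMR, VO2, VCO2 | none |
| Respiratory | VE, FeO2, FeCO2 | none |
| Resources spent | fat, carbohydrate, protein | none |

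That makes 3 + 3 + 3 = 9 variables, of which 0 are heart rate, heart-rate variability or blood pressure.

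**Step 2: the protocol's own rationale against the list.** C.2 names five responses to imagery. Oxygen consumption and metabolic rate are on the outcome list. Heart rate, blood pressure and respiratory rate are not, and no reason is given. So 2 of 5 are carried forward, and both are metabolic.

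**Step 3: the full-scale figure.** The total reproduces: 3 × 63 = 189. The 63 itself cannot be reproduced, because the heart-rate difference, its SD and the power are not given. The effect it implies can be found by assuming two-sided alpha 0.05 (stated in C.3.9 for the analysis, not for the sizing) and a two-group comparison of means:

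n per group = 2 (z₀.₉₇₅ + z_power)² / d², so d = √(2/63) × (z₀.₉₇₅ + z_power)

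- 80% power: √(2/63) × (1.960 + 0.842) = 0.50
- 90% power: √(2/63) × (1.960 + 1.282) = 0.58

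On the 80% assumption, the required size depends on the standardised heart-rate difference as follows:

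| d | n per group | three groups |
|---|---|---|
| 0.40 | 99 | 297 |
| 0.45 | 78 | 234 |
| 0.50 | 63 | 189 |
| 0.55 | 52 | 156 |
| 0.60 | 44 | 132 |

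An error of 0.1 in d moves the total from 189 to 297 or 132. The SD of heart rate in this setting is what the pilot could contribute to judging d, and as listed it would not supply it.

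**Step 4: does the same gap affect the pilot's size?** No. The pilot's 15 per group is attributed to recommendations for pilot studies. The heart-rate figure enters only through the 10% rule: 0.10 × 189 = 18.9 in total, or 6.3 per group. That is below the cited minimum of 12 per group and below the chosen 15. The planned 54 then follows as 15 × 1.2 = 18 per group and 3 × 18 = 54. None of these steps depends on which autonomic outcome is collected.

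**The case against.** The strongest reply is that the proxy is declared openly. The protocol says that metabolic rate is used as an indicator, and C.2 introduces the study with the idea that imagery may alter metabolic responses. Oxygen consumption and metabolic rate are among the responses it names, and both are measured. A reader of the results can see exactly what was recorded. This stands as a point about transparency. It does not supply the missing link from resting metabolism to autonomic function, and C.2 itself lists metabolic rate beside heart rate and blood pressure as separate responses.

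A second reply is that the protocol nowhere promises to re-estimate a variance for the full-scale study. That is correct. The feasibility section names the target sample size only in general terms. The loss is therefore that the pilot cannot inform the full-scale figure, not that a stated objective fails.

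Some stronger readings are tempting, but the documents do not support them:

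- A reader might infer that no outcome in the trial matches its aims. The imagery questionnaire, mental chronometry and hand laterality test serve aim 2, and the feasibility criteria stand on their own. The mismatch is confined to aim 1.
- A reader might infer that heart rate will not be recorded. The text does not say so. ECG monitoring appears as a device feature with no statement on its use, so heart rate is unlisted rather than excluded.
- A reader might infer that the nine variables are largely redundant with one another. The documents give nothing to establish this, and the point does not need it.

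**Conclusion.** The concern holds for aim 1. All nine measures listed for it are metabolic, ventilatory or substrate variables, and their use as an indicator of autonomic function is asserted without justification. On their own they cannot carry a conclusion about autonomic function in either direction. It would go too far to say that they are irrelevant to it: the documents show an unjustified proxy, not a disproved one.

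Heart rate underlies the full-scale 63 per group (189) and is not a listed outcome, so the pilot as written cannot inform that number. The implied standardised difference of 0.50 or 0.58 rests on assumed power of 80% or 90% and two-sided alpha 0.05. The conclusion about the outcome does not depend on those assumptions. The size of the pilot is not in question.

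The matter should be settled before data collection, because an outcome that was not recorded cannot be recovered afterwards.

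**What to change.** In C.3.7, add resting heart rate, taken from the device's integrated ECG during the 15-minute supine rest already planned, before and after training, and name it as an aim 1 outcome. Add a heart-rate-variability index only if the device can export beat-to-beat data, which the protocol does not state. Label the nine existing variables as metabolic and respiratory outcomes.

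If the ECG will not be recorded, restrict aim 1 in C.2 and the conclusions drawn from it to resting metabolic and respiratory responses, and base the full-scale sample size on one of those variables instead of heart rate.

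The first option costs electrode placement and some extra data handling, with no added visit or device. The second costs a narrower claim and a new full-scale calculation.
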